### Missing data

We assumed a 10% loss to follow-up among the population that completed the trial and enlarged the sample size from 200 to 220 participants.

### Blinding

Assessors will be blinded. However, the blinding of investigators and participants (masking of intervention) to the use of PN is not feasible. We do not anticipate any requirement for unblinding but, if required, investigators will have access to group allocations and any unblinding will be reported.

### Post-trial care

Conventional intensive care therapy will be continued according to the discretion of the intensivist.

### Harms and benefits

#### Potential burdens and risks, expected benefits

Potential adverse events and risks related to PN include, but are not limited to, infections (e.g. catheter-related infections), hyperglycaemia, refeeding syndrome, diarrhoea and liver dysfunction (e.g. bile sludge and cholestasis). The study protocol is designed in compliance with the present recommendations of ASPEN and ESPEN on optimal nutrition care in patients after surgery. The strategies used in both arms are classified as standard care; therefore, for example, adverse events associated with routine medical invasive procedures, such as central venous catheter placement, will not be treated as any study-related risks. There will be no special criteria for discontinuing or modifying allocated interventions. There is no anticipated harm and compensation to those who suffer harm from trial participation. The benefits of SPN for patient recovery are well documented. Complementary to previous studies, the results of this trial might elucidate the optimal timing of SPN in patients recovering from oncological gastrointestinal tract surgery in the long-term setting.

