#### Route of administration

SPN is continuously infused for 24 h via central venous catheter. The central venous catheter is placed for routine medical purposes and therefore is not a part of any study-related procedure.

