1. ICU patients in the acute phase of critical illness after gastrointestinal oncological surgery 2. Age ≥18 years 3. Central venous access available for continuous infusion of the study drugs 4. Admitted to the ICU during the previous 24 h with a minimum expected ICU stay of ≥5 days 5. Sequential Organ Failure Assessment (SOFA) score ≥ 2 6. Written informed consent from the patient or the patient’s legal representative	Exclusions associated with nutritional status: 1. Received parenteral nutrition within 7 days before randomisation 2. Expected to receive ≥20% of energy via supplemental EN and/or non-nutritional sources (e.g. glucose solution for drug dilution or lipids from propofol) during the first 3 nutritional treatment days 3. Inability to initiate EN prior to randomization 4. Body mass index <17 kg/m^2^ or >35 kg/m^2^ 5. Any congenital errors of amino acid metabolism Exclusions associated with comorbidities and allergies: 6. Known hypersensitivity to fish, egg, soybean proteins, peanut proteins, or to any of the active substances or excipients contained in SPN 7. Known hypersensitivity to milk protein or to any other substance contained in SPN 8. Hemophagocytic syndrome 9. Known history of HIV, hepatitis B and/or C 10. Any severe, persistent blood coagulation disorder with uncontrolled bleeding Concomitant therapy exclusions: 11. Chronic maintenance therapy with systemic glucocorticoid steroids (hydrocortisone >0.3 mg/kg/d). 12. Concomitant administration of chemotherapy 13. Administration of growth hormone and teduglutide within the previous 4 weeks	Laboratory exclusions: 14. Hypertriglyceridemia characterised by serum triglyceride levels >4 mmol/L (>350 mg/dL) 15. Treatment-refractory, clinically significant major abnormality in the serum concentration of any electrolyte (sodium, potassium, magnesium, total calcium, chloride, inorganic phosphate) 16. Acute liver failure with encephalopathy, including intoxication (e.g. paracetamol, death cap, golden chain) and/or liver enzymes (aspartate aminotransferase, alanine aminotransferase, gamma glutamyl transferase) or bilirubin exceeding 10 x upper limit normal Other exclusions: 17. Chronic liver failure (Child-Pugh scale B or C), e.g. secondary to drug or alcohol abuse 18. Participation in another interventional clinical trial within the previous 4 weeks 19. Pregnancy or lactation 20. Previous inclusion in the present study 21. Patient unlikely to survive to 6 months due to underlying illness 22. Receiving end-of-life-care

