### Evaluations and reporting of adverse event

If any adverse event or serious adverse event occurs, the Principal Investigator will be informed immediately. The duty of the Principal Investigator is to record these in the patient’s requisition form and inform the Local Ethical Committee in order to establish the causal relationship between the event and trial interventions. Adverse events will be reported in the study publication.

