## Discussion

Survival of critical illness and ICU mortality have been reduced in the last 10 years; however, the number of patients going to rehabilitation after ICU stay has tripled [10].

The factors that may influence the deterioration of physical quality of life after ICU need to be identified. A population particularly vulnerable to impairment in functioning after ICU stay are patients following expanded surgery of the gastrointestinal tract. Rapid development of national preventive and screening programmes have enabled early identification of resective gastrointestinal tumors, increasing the number of patients scheduled for that type of surgery. Nutritional support plays a major role in the recovery after extensive resections of the gastrointestinal tract. ESPEN and ASPEN recommend initiation of feeding via the EN route. However, early meeting of full nutritional requirements is rarely viable via the EN route alone, while adequate delivery of proteins might prevent the cascade of catabolism during the first days of ICU stay after extended surgery. Extensive muscle wasting may be a consequence of prolonged catabolic state. SPN is recommended when EN is not able to fulfill the daily nutritional requirements of those patients. Nevertheless, the optimal timing for introduction of SPN remains elusive. ESPEN guidelines suggest the introduction of SPN in first 7 days, while ASPEN recommends waiting until day 8. The a previous large trial, EPaNIC-NEJM, showed higher risks of adverse events after early introduction of SPN versus late introduction. It also showed no influence on mortality rate in either group. However, the issue of long-term quality of life was not covered discussed. The EAT-ICU trial [9], which was the only study investigating physical quality of life of the general population of patients after ICU, showed no improvement in PCS SF-36 in the group where early goal-directed nutrition was implemented. We hypothesize that early initiation of full nutritional support could significantly influence the physical quality of life of patients after oncological surgery of the gastrointestinal tract, a group of patients who are particularly vulnerable to the mixed catabolic effect of cancer and extensive surgery. Postsurgical patients admitted to the ICU constituted only 6% of the population studied in the EAT-ICU trial.

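### The harms section anticipates no harm and rules procedure-related events unrelated in advance, which conflicts with its own risk list, the adverse event section and the Discussion

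*Protocol article*

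**What the plan says.** All statements are in the protocol article.

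- **Potential burdens and risks, expected benefits.** The section opens with "Potential adverse events and risks related to PN include, but are not limited to, infections (e.g. catheter-related infections), hyperglycaemia", then adds refeeding syndrome, diarrhoea and liver dysfunction. It states that the design complies with ASPEN and ESPEN recommendations and that both strategies count as standard care. From this it concludes that "adverse events associated with routine medical invasive procedures, such as central venous catheter placement, will not be treated as any study-related risks". It then says: "There is no anticipated harm and compensation to those who suffer harm from trial participation".
- **Evaluations and reporting of adverse event.** "If any adverse event or serious adverse event occurs, the Principal Investigator will be informed immediately". The investigator records the event and informs the Local Ethical Committee so that its causal link to the trial interventions can be established. Adverse events are to appear in the publication.
- **Discussion.** A previous large trial "showed higher risks of adverse events after early introduction of SPN versus late introduction". On guidelines, ESPEN is said to suggest starting SPN within the first 7 days, whereas "ASPEN recommends waiting until day 8".
- **Route of administration and Table 1.** "SPN is continuously infused for 24 h via central venous catheter". The catheter is described as placed for routine purposes and not as a study procedure. Table 1 nevertheless makes this an inclusion criterion: "Central venous access available for continuous infusion of the study drugs".

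**The concern.** A harms section has to give a risk statement that the rest of the document supports, and a rule for relatedness that site staff can follow. This one does neither cleanly. It lists risks and then anticipates none. It also decides relatedness for a whole class of events before any of them has occurred, while the next section asks for a causality judgement on every event.

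The argument for the exclusion is that both arms are standard care. That does not settle relatedness here. The trial randomises the timing of SPN, so what matters is whether an event can be caused by being in one arm rather than the other. Two accepted strategies can still differ in the harm they cause.

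At stake are the labelling of central-line complications that occur after randomisation and the accuracy of the risk statement that ethics committees and readers rely on. The primary analysis is not affected.

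**Working it through.** No arithmetic applies: the document gives no harm rates, and the point is one of consistency. The check sets the statements side by side.

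1. **Anticipated harm against the section's own list.** The section names catheter-related infection, hyperglycaemia and other risks of PN, then says that no harm is anticipated. Both cannot stand as written.

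2. **Anticipated harm against the Discussion.** The earlier large trial compared early with late SPN, which is the contrast randomised here, and is reported as showing more adverse events with early SPN. The harms section does not mention it.

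3. **Guideline compliance against the Discussion.** The early arm starts SPN on day 1 and the control arm on day 7, if needs are not already met enterally. The Discussion attributes a day-8 recommendation to ASPEN, and neither start day matches it. The Abstract attributes a start between the first and seventh day to both societies. The Abstract, the harms section and the Discussion therefore disagree on what the guidelines say or on whether the design complies. Which is correct cannot be decided from the document.

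4. **Advance exclusion against case-by-case causality.** The adverse event section covers any event and sends it for a causality judgement. The harms section answers that question in advance for events of routine invasive procedures. Staff cannot apply both rules to the same event.

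5. **Scope of the exclusion.** Catheter placement is given only as an example, so the boundary is not defined. Catheter-related infection is attributed to PN in the same section, so the consistent reading leaves it outside the exclusion. Insertion, replacement and re-insertion fall inside.

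6. **Can allocation affect the excluded events?** For the first line, probably not: central access is required of every patient at entry and is said to be placed for routine care. For later lines, it can. Within the first 7 days, SPN is planned on up to 7 days in the early arm and on at most 1 (day 7) in the control arm, and it runs continuously through the line. A line that fails or is no longer otherwise needed may have to be replaced, kept or re-inserted for SPN, and the timing of that need differs by arm.

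7. **What is captured regardless of relatedness?** Catheter-related infections and bacteraemia are recorded, as are insertion and removal dates of central catheters, up to day 28 or discontinuation (Treatment and support in-hospital data). New hospital-acquired infection, insulin dose, blood glucose and phosphorus are secondary endpoints. Liver tests are done daily on days 1 to 7. Non-infectious line complications have no dedicated measurement beyond general adverse event reporting.

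Steps 1 to 4 are contradictions in the text. Steps 5 to 7 narrow the practical consequence to non-infectious complications of line procedures after randomisation.

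**The case against.** The strongest reply is that nothing is lost. Any adverse event is to be recorded and sent for a causality judgement, and publication is not limited to related events. A Data Monitoring and Ethics Committee reviews accumulating data annually. Infection, the main catheter harm, is compared between arms as a secondary endpoint, and a relatedness label cannot remove it. The exclusion names placement, which both arms share at entry. The sentence on anticipated harm also deals with compensation and is awkwardly built, so it may be a loosely worded formula rather than a considered risk statement.

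Most of this stands, and it rules out three stronger readings.

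- A reader might infer that harms of early SPN will be undercounted in general, or that the published comparison will look safer than it is. The recording and publication provisions do not support that.
- A reader might try to size the problem by the extra days of SPN-driven line use in the early arm. That counts line use, not misclassified procedure events. It also ignores that every control patient has central access at entry and that eligibility requires an expected stay of only at least 5 days.
- A reader might infer that the earlier trial's excess consisted of catheter events, or that unblinded site staff alone decide relatedness. The Discussion does not say what the excess events were, and the adverse event section involves the ethics committee.

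The reply does not remove the contradictions. The exclusion still pre-empts the causality judgement for replacement and re-insertion, and the risk statement still disagrees with the list above it and with the Discussion.

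**Conclusion.** The point holds as a conflict between stated rules, with a limited consequence. The harms section contradicts its own risk list, the adverse event section and the Discussion. The resulting risk is misattribution of complications of central-line placement, replacement or re-insertion after randomisation. It cannot be sized, because the document gives no rate of line replacement or of procedural complications in either arm.

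The verdict rests on two assumptions: that some lines are replaced or re-inserted after randomisation, and that SPN is sometimes the reason. If neither happens, no event is mislabelled, but the risk statement and the guideline claim still need correcting. The change is worth making because it is cheap and gives a consistent safety rule.

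**What to change.** 1. Delete the advance exclusion of procedure-related events, so that the adverse event section applies to every event in both arms.
2. Replace the sentence on anticipated harm with one that agrees with the listed PN risks and states that an earlier large trial reported more adverse events with early than with late SPN. State the compensation arrangement in a separate sentence.
3. Reconcile the guideline-compliance claim in the harms section with the Discussion and the Abstract. This concerns the description of the guidelines and the compliance claim; no change to the nutrition schedule is proposed.
4. Report all adverse events by arm regardless of judged relatedness, including central-line complications after randomisation. The insertion and removal dates already collected give line exposure and show replacements and re-insertions.

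The cost is a wording amendment, which needs acceptance by the Local Ethical Committees, and a few case report form fields for non-infectious line complications. The downside is that a few more events will be reported and the stated risk will look less favourable.

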### Evaluations and reporting of adverse event

If any adverse event or serious adverse event occurs, the Principal Investigator will be informed immediately. The duty of the Principal Investigator is to record these in the patient’s requisition form and inform the Local Ethical Committee in order to establish the causal relationship between the event and trial interventions. Adverse events will be reported in the study publication.

### Monitoring

Independent monitoring of adherence of the investigators to Good Clinical Practice regulations and of the data collection process will be held every 6 months. The Data Monitoring and Ethics Committee will review confidential interim analyses of accumulating data annually.

### Confidentiality

#### Data management

All actions will be undertaken to ensure anonymity of the trial participants. Patient data will be collected on paper sheets and later uploaded to the study database, which will not contain identifiable personal information. Access to the study password-protected database will be granted exclusively to the investigators and study statisticians. Storage of any study-related information on portable memory devices will be minimised. Collected paper data will be stored in a designated archive. Printed and electronic data obtained for study purposes will be kept for 5 years from the time of publication and later disposed of. Polish and EU legal regulations regarding medical data storage will be followed. The procedure of data management will be audited by the Principal Investigator.

#### Protocol amendments

Changes to the study protocol will have to be accepted by the Local Ethical Committees of the participating centers. Recruitment of the study participants will begin only when the final study protocol is assessed and approved Additional file 1.

#### Dissemination policy

We plan to share the results of our study with the scientific and clinical community by reporting it at conferences and by submission to a scientific journal for publication.

## Discussion

Survival of critical illness and ICU mortality have been reduced in the last 10 years; however, the number of patients going to rehabilitation after ICU stay has tripled [10].

The factors that may influence the deterioration of physical quality of life after ICU need to be identified. A population particularly vulnerable to impairment in functioning after ICU stay are patients following expanded surgery of the gastrointestinal tract. Rapid development of national preventive and screening programmes have enabled early identification of resective gastrointestinal tumors, increasing the number of patients scheduled for that type of surgery. Nutritional support plays a major role in the recovery after extensive resections of the gastrointestinal tract. ESPEN and ASPEN recommend initiation of feeding via the EN route. However, early meeting of full nutritional requirements is rarely viable via the EN route alone, while adequate delivery of proteins might prevent the cascade of catabolism during the first days of ICU stay after extended surgery. Extensive muscle wasting may be a consequence of prolonged catabolic state. SPN is recommended when EN is not able to fulfill the daily nutritional requirements of those patients. Nevertheless, the optimal timing for introduction of SPN remains elusive. ESPEN guidelines suggest the introduction of SPN in first 7 days, while ASPEN recommends waiting until day 8. The a previous large trial, EPaNIC-NEJM, showed higher risks of adverse events after early introduction of SPN versus late introduction. It also showed no influence on mortality rate in either group. However, the issue of long-term quality of life was not covered discussed. The EAT-ICU trial [9], which was the only study investigating physical quality of life of the general population of patients after ICU, showed no improvement in PCS SF-36 in the group where early goal-directed nutrition was implemented. We hypothesize that early initiation of full nutritional support could significantly influence the physical quality of life of patients after oncological surgery of the gastrointestinal tract, a group of patients who are particularly vulnerable to the mixed catabolic effect of cancer and extensive surgery. Postsurgical patients admitted to the ICU constituted only 6% of the population studied in the EAT-ICU trial.

This is a multi-center, single-blinded, prospective randomised study designed to establish the influence of early SPN on the long-term quality of life of patients admitted to the ICU after oncological surgery of the gastrointestinal tract. The potential benefits of this trial would include not only identification of factors that could alter the rate of individual physical impairments but, moreover, it might address the issue of growing costs of rehabilitation of ICU survivors to the healthcare system. Potential limitations of this study would include lack of masking of the assigned intervention. Another drawback of this study protocol includes the fact that a proportion of patients after major gastrointestinal oncological surgery is not routinely admitted to the ICU. Thus, the results of the study may have limited generalisability to patients admitted postoperatively to the ICU. We addressed this limitation by identifying the proportion between the whole cohort of patients who underwent major gastrointestinal oncological surgery to those included in the trial. We set the follow-up period at 3 and 6 months due to the fact that the definitive answer to the question about physical functioning after ICU can be established only after returning to the original home setting, while hospitalisation of cancer patients is prolonged on many occasions Additional file 1.

## Abbreviations

ASPEN: American Society of Enteral and Parenteral Nutrition
CRRT: continuous renal replacement therapy
EN: enteral nutrition
ESPEN: European Society of Enteral and Parenteral Nutrition
ICU: intensive care unit
PCS: Physical Component Score
PN: parenteral nutrition
SF-36: 36-Item Short Form Health Survey
SOFA: Sequential Organ Failure Assessment
SPN: supplemental parenteral nutrition
